#### Data Analysis

HR and raw ECG data will be analyzed using MATLAB (the MathWorks). Infant demographics will be analyzed using summary statistics. Continuous variables will be expressed as mean (SD) values, and categorical variables will be expressed as numbers (percentages), unless otherwise stated. The HR from HRD will be compared to PO or ECG using a paired *t* test. The Bland-Altman method will be used to compare the HR derived from each device—the HRD and the PO or ECG monitor, used as reference. The correlation between devices will be assessed using Pearson *r* statistic. Data will be first analyzed using all data points available, and outliers will be defined as 20 beats per minute rate difference between the methods. These discrepancies will be further analyzed to find the likely reason for deviation, including reexamination of the video recordings.

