## Introduction

### Background

Each year, over 10 million newborns require resuscitation worldwide, representing more than 10% of all global births [1]. Neonatal resuscitation is the set of interventions at the time of birth to support the establishment of breathing and circulation. These interventions include providing warmth to the infant using a heat source, placing the head in a sniffing posture with neck flexion and upper cervical extension (a position to open the airways), drying the infant, and simulating breathing. Multiple metrics—respiration, infant color, and heart rate (HR)—are measured every 30 seconds to ensure successful neonatal resuscitation [2]. Out of these indicators, HR is identified as the most important for an effective resuscitation process [3]. HR guides decision-making and escalation of care, including positive pressure ventilation, endotracheal intubation, chest compressions, and administration of epinephrine.

Despite the importance of HR in neonatal resuscitation, HR determination is challenging due to a lack of evidence regarding the most rapid and accurate method to assess it. Clinically accepted methods of HR assessment include pulse palpation (umbilical, brachial, and femoral), auscultation with a stethoscope, pulse oximetry (PO) monitoring, and 3-lead electrocardiogram (ECG) monitoring [2]. It is important to note that neonatal resuscitation efforts should be performed within the first minute of life, known as the “golden minute,” to ensure a high success rate and avoid neurodevelopmental disorders and hypoxic injury [4].

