#### Data Collection

The displayed HR from the HRD and the PO or ECG monitor will be video recorded for 3 minutes within the same video frame, as shown in Figure 1. Video recording will take place using a dedicated research digital camera mounted on a stand. Video recording will start once the infant is settled and the PO or ECG readings are stable. Stable readings are defined based on the device’s instructions on waiting for an appropriate amount of time after sensor placement for clinical HR determination. The HRD will then be placed on the infant’s chest until a consistent HR is displayed for 3 minutes, at which point video recording will start. After 3 minutes, the HRD will be removed, and then, the recording will be stopped. After the recording is completed, the entire HRD, including electrodes, will be wiped down with a surface disinfectant towelette (CaviWipe; Metrex). HRD device failure will be considered if no HR is displayed on the HRD within 60 seconds of application to the thorax.

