#### Data Management

Video recordings will be individually analyzed by 2 health professional researchers to determine the time it takes to apply the HRD to the thorax and the time from HRD placement to a steady HR display. Each researcher will review and record the HR from the HRD and PO or ECG at 2-second intervals for 3 minutes, providing approximately 90 HR notations per device per patient. For 50 newborns, the total number of HR annotations will be approximately 4500 data points. This will result in multiple HR data points to compare. To avoid human error in the annotation process, discrepancies in the HR of more than 5 beats per minute between the 2 researchers will lead to a reexamination of the video recordings until a consensus can be reached regarding the correct HR. The annotations from the 2 researchers will be averaged for the subsequent analyses.

Additionally, the HRD will record raw ECG signals for the duration of the device being in contact with the infant. Raw ECG data will be collected at 500 Hz sampling rate and transmitted to a research-dedicated laptop. The raw ECG and HR information from the HRD will be stored on different CSV files with a randomized identification number.

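### Agreement is analysed without reference to time since placement, and the recording start is contradictory, so no planned result shows whether the heart rate displayed soon after chest contact is accurate

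*Protocol article*

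**What the plan says.** **Readings.** Under Data Management (Protocol article), two researchers note the rate from each device "at 2-second intervals for 3 minutes, providing approximately 90 HR notations per device per patient". It adds: "For 50 newborns, the total number of HR annotations will be approximately 4500 data points".

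**Agreement.** Under Data Analysis, "The Bland-Altman method will be used to compare the HR derived from each device", with a paired t test and Pearson correlation alongside. The analysis set is given as: "Data will be first analyzed using all data points available". Outliers are set at a difference of 20 bpm between the devices, and the only follow-up named is a review of those discrepancies, including another look at the video. Time since placement does not appear.

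**Speed.** Data Management has the researchers read from the same video the time taken to apply the device and "the time from HRD placement to a steady HR display". Data Collection counts a device failure if nothing is displayed within 60 seconds of application.

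**Recording start.** Data Collection says "Video recording will start once the infant is settled and the PO or ECG readings are stable", and that the HRD is placed after that. The next statement on timing starts the recording only once the HRD has shown a consistent rate for 3 minutes.

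**Purpose.** The Background says that "neonatal resuscitation efforts should be performed within the first minute of life". The abstract's conclusions say the study examines how quickly the HRD gives a reliable rate. Study Significance and Impact likewise joins quick detection with accuracy.

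**The concern.** The stated purpose joins two properties: the rate should appear quickly, and it should be right when it appears. The plan measures them apart. The speed outcomes record when a display appears or settles, and a display can be steady and wrong. The accuracy outcome compares values with the reference but has no time axis. The result that would connect them, agreement in the early seconds of contact, is not among the planned outputs.

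The effect depends on which recording start is followed. With a start before placement, early readings enter the agreement analysis but are outnumbered by later ones. With a start after a consistent display, they never enter, and the pairs analysed come only from periods when the device was already performing steadily. The second start also cannot be squared with reading application time and time to steady display from the video, because both events would precede the recording.

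At stake is what can be said about rapid detection. A 3-minute agreement figure could be read as describing the first readings a clinician would see, when it mostly or wholly describes later ones.

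**Working it through.** **1. The plan's own figures.** 180 s / 2 s = 90 readings per device per infant; 50 × 90 = 4,500. Both reproduce.

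**2. Share of early readings, if the 3-minute window opens at placement.**
- First 60 s: 30 of 90 = 33%, or 1,500 of 4,500 overall.
- First 30 s: 15 of 90 = 17%.
- These are upper bounds. If the HRD is blank for the first t seconds, those intervals cannot form pairs, and the first-minute share is (60 − t)/(180 − t):

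| First display at t (s) | First-minute share of pairs |
|---|---|
| 0 | 30/90 = 33% |
| 10 | 25/85 = 29% |
| 20 | 20/80 = 25% |
| 30 | 15/75 = 20% |
| 45 | 7.5/67.5 = 11% |
| 60 | 0/60 = 0% |

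**3. Share of early readings, if recording opens after a consistent display.** Readings before the display settled supply 0 of 90.

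**4. Size of dilution under the first start.** The article gives no bias or SD for the differences, so every SD and bias below is an assumption.

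With zero bias, pooled SD = √[(n₁s₁² + n₂s₂²)/(n₁ + n₂)], and the limits are ±1.96 × SD.
- Early = first 30 s, SDs 20 and 5 bpm: √[(15 × 400 + 75 × 25)/90] = √87.5 = 9.35. Pooled limits are ±18.3 bpm, against ±39.2 early and ±9.8 later.
- The same split with early SD 15: √[(15 × 225 + 75 × 25)/90] = 7.64. Pooled ±15.0, against ±29.4 early.
- Early = first 60 s, SDs 15 and 5: √[(30 × 225 + 60 × 25)/90] = 9.57. Pooled ±18.8, against ±29.4 early.

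In the first of these cases, assuming normality, 31.7% of early differences exceed the plan's 20 bpm mark. Late exceedances are negligible, so the pooled share is 15 × 0.317/90 = 5.3%.

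With an early bias b, early share w and no late bias, pooled bias = wb and pooled variance = ws₁² + (1 − w)s₂² + w(1 − w)b². For b = 10, s₁ = 10, s₂ = 5 and w = 1/3:
- bias = 3.3 bpm;
- SD = √(33.3 + 16.7 + 22.2) = 8.50;
- limits −13.3 to 20.0, against −9.6 to 29.6 early.

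Under the second start w = 0. The same device would show bias 0 and limits ±9.8, with the early error absent altogether.

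**The case against.** The strongest reply has five parts.

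- **Separate questions.** The Objectives section asks how fast and how accurate as two questions, and speed has its own measures. This is fair, but the abstract's conclusions join them, and neither speed measure tests whether the value is correct.
- **No evidence of worse early accuracy.** The interval before a steady display may be blank rather than wrong. This stands in full: the document shows only that a settling period is expected, and the SDs above are illustrations.
- **The 20 bpm review would catch it.** In the first illustration, about 5.3% of 4,500, or some 240 readings, would be re-examined, and clustering at the start would probably be noticed. That helps under the first recording start, but it is an inspection of causes and gives no early estimate of bias or limits. Under the second start there is nothing early to inspect.
- **Article detail.** Time-stratified tables are often left to a fuller plan, and the word first in Data Analysis leaves room for more. That lowers the weight of the point. The contradictory recording start is in the text itself, however, and further analysis cannot recover readings that were never recorded.
- **Later readings matter too.** The Background describes rate checks every 30 seconds during resuscitation, so readings after the first minute are relevant. Agreed; the full 3-minute summary should stay.

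A reader might go further and infer that a device with poor early accuracy would be passed as acceptable for resuscitation. The documents do not support that. No acceptance limit is stated, so ±18.3 bpm is neither a pass nor a fail. Study Design leaves resuscitation use to later versions and studies. The golden minute is the first minute of life, whereas these infants are at least 24 hours old.

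**Conclusion.** The point holds as a modest, inexpensive improvement joined to a contradiction that has to be resolved in any case. As written, the plan yields no estimate of accuracy soon after contact. The first 60 s contribute at most one third of the readings under one recording start, and readings before a consistent display contribute none under the other. The second case is the worse one, and its source is the recording rule in Data Collection rather than the pooling in Data Analysis.

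The one-third bound follows from the document alone, provided the 3-minute window opens at placement. The amount of dilution does not: it rests on assumed SDs and biases, and would be nil if early and late accuracy were the same. Dilution cannot be taken as certain, and the first minute of contact in these infants is only a stand-in for the first minute of life.

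**What to change.** 1. Reconcile Data Collection with Data Management so that the camera runs from before the HRD is placed. The two timing outcomes already require this.
2. Give each reading its time from chest contact, and count intervals with no HRD display separately.
3. In Data Analysis, report bias and limits of agreement for the first 60 s after contact separately from 60-180 s, with 0-30 s and 30-60 s shown apart if numbers allow, beside the full 3-minute summary.
4. Base any statement about rapid detection on the early window, and state that contact time at 24 hours of age or later only stands in for the first minute of life.

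**Cost.** If recording already begins before placement, this is one extra table from readings already annotated. If practice has followed the other start, the recording procedure must change. Early reference values for infants already recorded would be missing, because reference rates are read from the video. The early limits rest on at most 1,500 of the 4,500 readings and may look less favourable.

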#### Data Maintenance and Security

Each infant will be assigned a participant identification number using a random number generator [20]. No personally identifying demographic information, such as name or parents’ names, will be collected. Confidentiality will be maintained throughout the study, in accordance with the Personal Health Information Protection Act. Paper-based data collected will be electronically transcribed into a CSV file. The paper-based data collection form will then be disposed in a confidential document bin at the hospital. The data, video recordings, CSV files with raw ECG data, the CSV files with infant demographics and characteristics as well as parental perceptions will be downloaded to a research-dedicated laptop for analysis. The data will be stored in a password-protected folder and will not be emailed nor transmitted on the web. Data transfer among the research team (the primary researchers) will occur through an encrypted flash drive, if necessary. The laptop will be stored in a locked cabinet in a locked room in the research lab at the university, with access provided to only the primary research investigators. All the study investigators will have access to all the data, except the consent forms, which will be only accessible by the principal investigator.

## Results

The study is currently ongoing. The projected end date for data collection is around July 2024.

## Discussion

This paper discussed a research protocol for conducting accurate and reliable HR estimation using a novel real-time HRD based on 3D-printed dry-electrode single-lead ECG signals. Recent advances in biomedical sensor and wireless information and communication technologies have enabled us to develop a novel HRD, aimed at potentially disrupting the traditional assessment of HR in neonatal resuscitation efforts. The rapid application, measurement, and display of HR on a device mounted directly on the neonate addresses significant gaps in the provision of optimal neonatal resuscitation. The main objective of this study is to examine the novel HRD’s ability and feasibility in obtaining an accurate HR in newborns, using dry electrodes, and comparing it to the state-of-the-art clinical-grade HR monitors at the hospital.

However, this study is limited to the feasibility of HR detection on a healthy population of newborns using dry electrodes, and it does not cover in-depth analytical metrics of ECG and HR for disease diagnosis. It is apparent that further studies should focus solely on ECG abnormalities in neonates, including bradycardia, pulseless electrical activity, and long QT syndrome. The work is also limited to the use of certain 3D-printed conductive plastic-based dry electrodes for single-lead ECG acquisition, limiting its applicability when ECG quality is compared to other dry-electrode materials, such as stainless steel and textiles. Furthermore, the proposal does not include clinical-grade ECG acquisition for comparison with the HRD’s raw ECG signals due to the restraints in obtaining access to HR monitor raw ECG information. In addition, the use of algorithms on clinical-grade devices cannot be accessed, limiting this work to the examination of HR information between the HRD and clinical HR monitors. However, the raw ECG obtained through the HRD can be used to derive novel hand-crafted features that assist in quick HR estimation and prediction using artificial intelligence.

Ideally, this study will lead to critical improvements in the HRD prototype’s accuracy and speed of detection, ensuring its robustness prior to further clinical testing. This preliminary work is essential to form the foundation of a larger programmatic endeavor to transform this HRD into a relevant and robust novel medical device for neonatal resuscitation efforts. It is critical that new clinical technologies be evaluated with methodologic rigor to help inform clinicians and parents on the reliability, feasibility, and ultimately, the effectiveness of new technologies. This is an early proof-of-concept study to assess the reliability of the value behind this HRD and its goals of ultimately saving infant lives through widespread clinical adaptation and implementation.

## Appendix

Multimedia Appendix 1 Recruitment script.

Multimedia Appendix 2 Data collection form.

## Abbreviations

CCHD: critical congenital heart disease
DS: digital stethoscope
ECG: electrocardiogram
HR: heart rate
HRD: heart rate detector
NICU: neonatal intensive care unit
PO: pulse oximetry
PPU: postpartum unit
